### The iNCK Intervention and Standard of Care Comparator

The iNCK includes a clean birth kit, 4% CHX topical gel, sunflower oil emollient, one ThermoSpot™ temperature monitoring sticker, a fleece blanket, a reusable instant heat pack warmer, three 200 μg dissolvable sublingual misoprostol tablets, a pictorial instruction guide, and a pictorial diary to mark daily use of iNCK components (Fig. 1). All of these components are packaged into a large resealable transparent plastic bag that is delivered by LHWs to enrolled participants in the intervention group. Additionally, each LHW assigned to the intervention group was provided with one handheld battery-operated scale to weigh newborns at their first post-delivery home visit. Table 1 provides a detailed description of the individual iNCK contents and their intended use.

**Fig. 1 Fig1:**
[figure not shown]
Contents of the iNCK, which includes: **A** Clean birth kit: Ai) Clean plastic sheet, Aii) surgical gloves, Aiii) maternity pad, Aiv) cotton balls, Av) cord clamp, Avi) antibacterial soap bar, **B** chlorhexidine 4% gel **C** three 200 μg misoprostol tablets, **D** sunflower oil emollient, **E** ThermoSpot™ sticker, **F** Click-to-heat warmer, **G** fleece blanket, **H** pictorial diary for documenting use of iNCK components, **I** pictorial guide, **J** battery-operated weighing scale (used by LHW)

**Table 1 Tab1:** Description of each iNCK component and its intended use

Kit content	Description and intended use
Clean birth kit (CBK)	**•**Sterile blade to cut the umbilical cord **•**Clean plastic sheet to be placed on the ground or **•**surface for birth **•**Plastic gloves to be worn by the birth attendant **•**Hand soap **•**Two cord clamps **•**Maternity pad to absorb peri- and post-natal bleeding **•**Ten cotton balls to apply CHX
Chlorhexidine (CHX)	**•**10 gm of 4% CHX topical gel, a broad-spectrum antiseptic, in a small plastic tube. CHX should be applied once per day from the first day of the baby’s life until day 10 of life
Misoprostol	**•**Three 200 µg dissolvable misoprostol tablets to be used prophylactically to prevent PPH. The tablets should be taken immediately after delivery of the baby and before delivery of the placenta. For participants who deliver via C-section, the attending clinician will decide whether or not to administer misoprostol
Sunflower oil emollient	**•**50 ml of sunflower oil emollient packaged in a small plastic bottle to massage over the newborn’s skin, avoiding the face and scalp. Sunflower oil emollient should be applied once per day from the first day of the baby's life until day 28 of life
ThermoSpot ™	**•**12 mm diameter round sticker that adheres to the skin and changes color based on body temperature. ThermoSpot™ should be applied to the baby’s neck over the carotid artery on the first day of the baby's life and left in place until day 14 of life
Fleece blanket	**•**One fleece blanket (65 × 86 cm), to wrap the baby along with the activated warmer whenever moderate to severe hypothermia is detected by ThermoSpot™
Warmer	**•**One reusable pocket-sized click-to-heat warmer that heats up to a temperature of about 50 °C and then gradually cools to ambient temperature over about 15 to 20 min. The warmer will be activated whenever moderate to severe hypothermia is detected by ThermoSpot ™
Pictorial guide	**•**A pictorial guide that illustrates how and when to use iNCK components
Pictorial diary	**•**The diary will enable self-reporting regarding compliance for individual iNCK components (i.e., If/when/how a component was used). Participants will tick boxes beside a series of images embedded in a calendar to indicate if she used a specific iNCK component on a given day. Each image contains a checkbox embedded in the upper right corner of the picture and corresponds to a day
Handheld battery-operated scale with a suspended cloth sling	**•**The scale will not be packaged within iNCK but will be distributed to LHWs in intervention clusters for measuring newborn weights, and prompting appropriate health facility visits for newborns found to be low birth weight (< 2500 g)

At the time of the third trimester delivery of the iNCK, the LHW will provide approximately 15–30 min of instructions to the pregnant women and other family members and caregivers who are present regarding the kit content and use. There were no further training sessions on how to use the iNCK delivered via the trial infrastructure; however, families had access to the pictorial iNCK instruction guide and could ask questions of LHWs during future household visits.

#### Clean birth kit (CBK)

Pregnant women will be instructed to provide the CBK to the birth attendant conducting the delivery, regardless of whether she delivers at home or at a facility. The CBK includes: i) Clean plastic sheet; ii) surgical gloves; iii) antibacterial bar of soap; iv) two cord clamps; v) maternity pad; and, and vi) cotton balls. A previous study in Pakistan reported a reduction in sepsis and neonatal mortality when combining CBK use with an educational component on how CBKs should be used [17]. A systematic review which included 37 studies (26 quantitative and 11 qualitative) from 15 countries (*N* = 48,767) found that the use of CBK was associated with a lowered occurrence of puerperal sepsis and a reduction in neonatal mortality [18].

#### Chlorhexidine (CHX)

The mother/caregiver will be taught to apply the CHX to a clean cotton ball and rub it on the newborn’s umbilical stump and the surrounding area, once per day, from the first day of the baby’s life until day 10 of life. In previous studies, the application of CHX to a baby’s umbilical cord showed a reduction in omphalitis and neonatal deaths in community settings [19, 20].

#### Misoprostol

The iNCK contains three 200 μg dissolvable misoprostol tablets. Mothers will be instructed to take the three tablets immediately after delivery of the baby and before delivery of the placenta to reduce the risk of PPH. For participants who deliver via C-section, the decision on misoprostol use will be deferred to the attending clinician. Data collectors will retrieve any unused misoprostol tablets from families at the home visit on day 29. Due to its low cost, oral route of administration, and no requirement for cold-chain storage, misoprostol can be used in low-income and remote settings and has been shown to be safe [21, 22].

#### Sunflower oil emollient

The mother/caregiver will be directed to massage a small amount of sunflower oil (Synergy Crafts, Karachi) onto the baby's skin all over their body, avoiding the face and scalp, once per day, from the day of birth until day 28 of life. In low-income countries, sunflower oil has been proven to be effective in preventing hospital-acquired infections in preterm neonates and supporting their critically compromised skin barrier [23].

#### Thermoindicator

The mother will be taught to place a ThermoSpot™ sticker (Maternova Inc, USA) over the carotid artery region of the newborn's neck on the day of birth and to use the sticker to continuously monitor the newborn’s body temperature until day 14 of life. She will be taught to reapply the sticker if it falls off before day 14. Additionally, she will be taught about the meaning of the different color responses, where a green face indicates normal temperature (36.5–37.5 °C), a pale green face indicates cold stress (36.0 °C–36.5 °C), a blue face indicates fever (> 39 °C), a red face indicates moderate hypothermia (35.0–35.5°C), and a black face indicates severe hypothermia (< 35°C). When the sticker turns pale green, the mother is educated to start kangaroo care, wherein she will place the baby skin-to-skin against her chest and monitor their temperature using the ThermoSpot™ sticker. Further, when the sticker turns red or black, the mother is instructed to place the newborn in the fleece blanket with the activated warmer and seek immediate medical care for the newborn. Caregivers will also be taught to seek immediate medical attention if the sticker turns blue, indicating that the baby has a fever. Several research studies have shown that ThermoSpot™ is effective in newborn temperature monitoring, especially in resource-limited areas [24, 25].

#### Fleece blanket and warmer

Whenever moderate to severe hypothermia is detected by ThermoSpot™, the mother is instructed to wrap the newborn with the provided, locally purchased, fleece blanket. The reusable instant heat pack warmer is to be activated when the ThermoSpot™ detects that the newborn is experiencing moderate or severe hypothermia. Inside the warmer is a small metal disk that, when flexed, begins a rapid exothermic crystallization reaction of the surrounding salt solution. Once activated, the contents of the warmer will begin to solidify and will increase in temperature to about 50 °C and then gradually cool to ambient temperature over a period of about 15–20 min. The solidified solution can later be returned to a liquid form by boiling the warmer in water.

#### Pictorial guide

A pictorial guide was developed locally to be culturally appropriate and contains non-written, step-by-step illustrations showing how to use the iNCK components. The pictorial guide is inserted into the resealable bag to ensure it remains with the iNCK and is not lost. The purpose of the pictorial guide is to improve compliance with the intended use of each iNCK component in a setting with low literacy rates.

#### Pictorial diary

The mother/caregiver will be provided with a pictorial diary to self-report their use of individual iNCK components using a simple check-box approach that does not require users to be able to write. LHWs will provide instructions on how to use the pictorial diary during the third trimester visit. The diaries will be collected from participants during the 29th-day visit.

#### Handheld battery-operated scale with a suspended cloth sling

LHWs will weigh the newborn during their first post-delivery home visit. The neonate will be weighed twice, and the average of these two weights will be recorded as the birth weight. The day on which the LWH measures the newborn’s weight will be recorded.

### Randomization

Covariate-constrained randomization was used to promote balance in key indicators associated with neonatal mortality between arms [26]. The randomization strategy considered: (1) cluster-level baseline NMR; (2) cluster-level baseline proportion of newborns delivered at a health facility; and, (3) GB study district (nominal categorical variable of the seven study districts). In December 2021, all clusters were randomized and allocated to either the intervention or control arm by a statistician who is not affiliated with the study, using the cvcrand package in R version 4.1.2 [27]. Balanced randomization schemes were defined as those where between-arm differences for baseline NMR were < 5%, baseline health facility deliveries were < 10%, and where at least 33% of clusters per district were allocated to each arm. The statistician then randomly selected one scheme from all balanced schemes (*n* = 11,041) using a random seed number.

### Delivery of the integrated neonatal care kit

As part of their routine activities, LHWs identify pregnant women and record the first day of their last menstrual period. As part of their mandate, LHWs already register all pregnant women in their catchment area within the first trimester of pregnancy. On a monthly basis, LHWs report the number of newly identified pregnancies to their Lady Health Supervisor (LHS).

To efficiently capture pregnancy data and enable timely iNCK delivery and subsequent data collection, our research team will provide LHSs across each of the seven districts with a pregnancy identification form to document the pregnant woman’s name, address, and phone number. LHSs will distribute these forms to LHWs, who will in turn complete them during home visits when they first identify new pregnancies. The information enables study-employed data collectors to locate the appropriate households to screen for eligibility, obtain written consent, and enroll participants, and for field supervisors to contact the mothers/caregivers directly to schedule data collection visits.

During this same visit, and after collecting written informed consent, LHWs will provide the iNCKs to participants in intervention clusters, educate them on how to use the kit components plus provide the local standard of care. The LHW will be directly observed during these activities by a trained data collector who will complete an evaluation of the process. Participants who reside in control clusters will not receive iNCKs but will receive the local standard of care from LHWs. To facilitate the timely and reliable notifications of new births, at the time of consent, all participants will be provided with contact information and instructions to notify the study team and/or their LHWs as soon as possible following delivery.

### Study outcome measures

The primary outcome measure is all-cause neonatal mortality, defined as the death of a live-born child from any cause within the first 28 days of life. Study outcomes (Table 2) will be measured on all enrolled participants.

**Table 2 Tab2:** Primary and secondary outcomes

Primary Outcome	**•**All-cause neonatal mortality among live born neonates in first 28 days of life
Secondary Outcomes	**•**Cumulative incidence of omphalitis
	**•**Cumulative incidence of post-partum hemorrhage (PPH)
	**•**Post-delivery health facility utilization by pregnant women, and/or neonates and mothers in the first month postpartum
	**•**Cumulative incidence of hypothermia within the first 28 days of life, as identified through use of the ThermoSpot™, and explore the seasonal variability (by month) in the cumulative incidence of hypothermia **•**Cumulative incidence of fever within the first 28 days of life, as identified through use of the ThermoSpot™
	**•**Compliance with instructions on how to use the iNCK
	**•**Cause-specific neonatal mortality as determined by verbal autopsy

### Data collection and data management

Data collectors who have a minimum qualification of a high school diploma will work independently from the LHWs to collect baseline and trial data. They will undergo a three day instructional training session covering the trial’s design, the iNCK components, and all data collection forms.

During the implementation of the baseline survey, data collectors visited selected villages from the included clusters, explained the purpose of the study to the sampled households, and administered baseline questionnaires, the results of which were used to calculate the region and cluster-specific NMRs and birth rates.

For the intervention phase of the trial, data collectors will complete one in-person at-home visit, a mid-point assessment call, and try for a second in-person at home visit. The first in-person visit will occur during the third trimester of pregnancy, at which time data collectors will screen potential participants for eligibility. If eligibility criteria are met, participants who provide informed consent to participate in the trial will receive a pictorial diary from the LHW to enable self-reporting regarding compliance for individual iNCK components (intervention clusters only). Data collectors will then administer a questionnaire in the form of a structured interview to collect sociodemographic and household data. On the 8^th^ day of a newborn's life, field supervisors will attempt to complete phone interviews with participant households to collect information surrounding the baby's delivery and study outcomes of interest that may have occurred during the first week of the newborn’s life. While efforts will be made to complete these calls on the 8th day of life, a one-week window will be permitted for completing this phone call (between the 8th day through the 14th day of the newborn’s life). If the study team is unable to contact the participant for this data collection touchpoint, data collectors will obtain this information during the in-person at-home visit on the 29th day of the baby’s life. Data collectors will visit participant households on day 29 of the newborn's life to collect information that will enable the assessment of primary and secondary outcomes related to neonatal and maternal health, and will collect the completed pictorial diaries and any unused misoprostol tablets from the participants before leaving. While efforts will be made to collect data on day 29, this in-person visit will be attempted up until day 43 post-natal age, if necessary. If, after two to three consecutive visits, the study team cannot reach a participant household by day 43, the day 29 questionnaire may be completed over the phone by the field supervisor that presides over the districts in which these participants live. However, if a participant cannot accommodate the time required to complete the questionnaires involved with the day 29 visit by phone or in person before or on day 43 of the newborn’s life, or if the participant is lost to follow-up following the notification of birth, a modified vital outcomes questionnaire will be administered to participants, if possible, either in-person or over the telephone, to confirm whether their baby survived the neonatal period.

In the event of a newborn death or stillbirth, data collectors will request permission to administer a verbal autopsy (VA) to ascertain the cause of death or stillbirth. The World Health Organization’s guidelines on the development and use of VA are being used in this study with adaptations for the local context [28]. A minimum 2-week mourning period will precede administration of the VA.

To manage and store data collection forms throughout the trial’s duration, a main hub office in Gilgit and a sub-hub office Skardu as well as and six "spoke" offices in Ghanche, Kharmang, Shigar, Nagar, Astore, and Diamer have been established to coordinate the collection of data and the transfer of completed data collection forms. All data will be collected on paper forms. Data collectors administer the questionnaires, collect completed forms and diaries from participants, and deliver these items back to the Skardu or Gilgit offices within one week of collecting data. Forms and diaries are transferred to the Skardu office from districts Ghanche, Kharmang, Shigar, and Skardu, while completed forms are transferred to the Giglit office from districts Nagar, Astore, and Diamer. To ensure data security, a supervisor or data collector will travel with the paper forms in a study vehicle and conduct an in-person handover process with the teams in Skardu and Gilgit. Upon receiving completed forms in each district office, the field supervisor will review them, and if a potential error is identified, will contact the data collector who interviewed the participant to assess and, if needed, reconcile the error and sign off on the accuracy of the form. Data entry specialists will assess the paper forms for completeness and consistency. If any issues are discovered, these will be discussed with the project team and respective field supervisors. The field supervisor will consult the original data collectors for possible explanations. All forms will be double-entered into a REDCap database and compared for errors. Discrepancies between the two entries will be reconciled by referring to the original paper forms.

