### Statistical analysis plan

Hypothesis testing for this study will be based on a superiority framework and will be conducted at the α = 0.05 significance level. Primary analyses will be conducted using a complete-case, intention-to-treat approach, where participants will be analyzed in the trial arm their cluster was randomized to, irrespective of contamination or adherence to instructions on how to use the iNCK. The unit of analysis will be the individual neonate (neonatal mortality, omphalitis, fever, hypothermia, and healthcare utilization for newborn morbidities) or the individual woman (PPH and healthcare utilization for PPH). Risk ratios for the primary (neonatal mortality) and secondary (omphalitis and PPH) outcomes will be estimated using multivariable modified Poisson regression [29], with generalized estimating equations to account for the clustered design and robust variance estimators to account for multiple births and/or multiple pregnancies during the study period. Analyses of neonatal mortality (the primary outcome) will adjust for newborn sex, antenatal care, and gestational age at birth to improve power and efficiency; calendar time to account for underlying temporal trends (defined as month of birth, setting month of study launch as month 0); and the covariates used in the randomization procedure: GB study district, log cluster-specific baseline NMRs, and the cluster-specific baseline proportion of children delivered at a health facility. Analyses of omphalitis (secondary outcome) will adjust for newborn sex, antenatal care, and GB study district. Analyses of PPH (secondary outcome) will exclude women who delivered via C-section, and will adjust for parity, maternal age, history of prior C-section, history of prior PPH, GB study district, and the cluster-specific baseline proportion of women who reported experiencing PPH. The frequency of hypothermia, cold stress, and fever detected by ThermoSpot™ within the first 14 days of life will be described amongst participants in intervention clusters only, overall and by calendar month to assess seasonality. Finally, the frequency and location of health facility utilization for omphalitis, PPH, hypothermia, and fever will be described using counts and proportions amongst individuals experiencing each respective morbidity and will be stratified by trial arm. The proportion accessing healthcare services by trial arm will be compared using clustered t-tests and modified Poisson regression.

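### As written, the enrolment questionnaire follows the diary hand-over, and by implication the kit teaching, in intervention clusters only; recalled history items such as prior PPH should be collected before hand-over

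*Protocol article*

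**What the plan says.** Data collection and data management describes a single in-person visit before birth. Data collectors screen for eligibility. Consenting women in kit clusters "will receive a pictorial diary from the LHW to enable self-reporting regarding compliance for individual iNCK components (intervention clusters only"). The next sentence reads: "Data collectors will then administer a questionnaire in the form of a structured interview to collect sociodemographic and household data".

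Three other places bear on the order:

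- Delivery of the integrated neonatal care kit: "During this same visit, and after collecting written informed consent, LHWs will provide the iNCKs to participants in intervention clusters". Education on the components follows, watched by a data collector. Control women receive the local standard of care and no kit.
- The iNCK Intervention and Standard of Care Comparator: the diary is listed among the kit contents, and "All of these components are packaged into a large resealable transparent plastic bag that is delivered by LHWs to enrolled participants". After Table 1, the teaching is tied to that hand-over: "At the time of the third trimester delivery of the iNCK, the LHW will provide approximately" 15 to 30 minutes of instruction.
- Pictorial diary: "LHWs will provide instructions on how to use the pictorial diary during the third trimester visit".

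On use of the data, the Statistical analysis plan section says that the PPH analysis "will adjust for parity, maternal age, history of prior C-section, history of prior PPH", plus district and a cluster-level baseline PPH proportion. The mortality and omphalitis models adjust for antenatal care. The per-protocol analyses match compliant kit-arm women to controls by propensity score.

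**The concern.** An individual covariate sharpens a comparison safely only if it is measured in the same way in both arms. If kit-arm women report their history after being taught about PPH and control women report theirs without that teaching, the answers may differ by arm for reasons unrelated to true history. A woman who has just heard why misoprostol is supplied may be readier to recall or label an earlier bleed as PPH.

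If that happens, adjusting for prior PPH makes the kit arm look higher-risk than it is and pulls the adjusted PPH risk ratio below its true value, in favour of the kit. The same items, if used for propensity-score matching, would carry the distortion into the per-protocol comparison. The baseline table would also be a weaker check on selective enrolment, which matters because enrolment follows cluster randomization.

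**Working it through.** **Order of steps.** No stated figure depends on the sequence, so the sections are set side by side.

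1. Stated: consent, then diary (kit clusters only), then questionnaire.
2. Stated: the diary is one of the components in the kit bag.
3. Stated: the teaching is given when the kit is delivered, and diary instruction is given at the third-trimester visit.
4. Stated: kit and education come in the same visit as consent, after it. Their position relative to the questionnaire is not given.
5. Inferred from 1 to 4: kit and teaching also precede the questionnaire. No sentence supports the reverse order.

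**Which items could be affected.**

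- Sociodemographic and household facts: largely insensitive to kit teaching.
- Newborn sex, gestational age at birth and month of birth (primary model): determined at birth, so not fixed at this interview under any order.
- Cluster-level baseline NMR and facility-delivery proportion: from the June to August 2021 survey, before the December 2021 randomization. The cluster-level PPH proportion is also a baseline figure, and that survey collected PPH.
- Last menstrual period: recorded by LHWs in routine work.
- Prior PPH, and possibly antenatal care: recalled and open to influence. Parity and prior C-section are less so. The article names no form for any of these four. It describes no individual interview before the enrolment visit; the other contacts are at day 8 and day 29.

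**Illustration for the PPH model.** All inputs here are assumptions; the article gives none of them. There is no kit effect and the arms are of equal size. True prior-PPH prevalence is p = 0.10 in both arms. History multiplies PPH risk by k. A further share d of kit-arm women is falsely recorded as having a history, so recorded prevalence in that arm is q = p + d.

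Take risk without history as 1. Expected events are then (1 − p) + pk in each arm, and 2pk + d among all women with recorded history. A Poisson log-link model with arm and recorded history reproduces these margins. With b the fitted history effect, the fitted arm risk ratio is

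RR = [(1 − p) + pb] / [(1 − q) + qb].

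Worked case, k = 3 and d = 0.05:

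- Events per arm: 0.90 + 0.30 = 1.20. Events with recorded history: 0.60 + 0.05 = 0.65.
- The margins are met at b = 2.62.
- RR = (0.90 + 0.262) / (0.85 + 0.393) = 1.162 / 1.243 = 0.935.
- Check: baseline rate 1.20 / 1.162 = 1.033, and 1.033 × 2.62 × (0.10 + 0.15 × 0.935) = 0.65.

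Adjusted RR when the truth is 1:

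| Over-reporting d | k = 2 | k = 3 | k = 4 |
|---|---|---|---|
| 2 points | 0.984 | 0.970 | 0.959 |
| 5 points | 0.964 | 0.935 | 0.911 |
| 10 points | 0.940 | 0.891 | 0.852 |

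At p = 0.05 and 5 points the range is 0.968 to 0.915. In the 10-point row at p = 0.10, half of the recorded kit-arm histories would be false, so that row is an extreme.

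**The case against.** The strongest reply is that this rests on one narrative word in a condensed article. Only the diary is explicitly placed before the questionnaire, and the questionnaire is described as covering sociodemographic and household data. Form contents belong to the full protocol, which is not shown. If prior PPH is asked elsewhere, the quoted sentence does not govern it. The over-reporting figures have no source in the article. Reordering would not blind the data collectors, who know the allocation in any case. Nor would it stop the teaching from influencing how the PPH outcome itself is reported after delivery.

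Much of this stands. It limits the point to a few recalled items and makes the size conditional. It does not remove the point, because the article states a sequence rather than leaving one out, and that sequence puts at least one arm-specific step before the interview. Asking prior PPH at day 8 or day 29 would not help, since both contacts come after the kit.

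A reader might infer that all individual baseline data are compromised, or that the primary mortality result is biased. The article supports neither. Most questionnaire items are stable facts. Three of the primary model's individual-level covariates are determined at birth. For the fourth, antenatal care, an influence is conceivable but no size is shown.

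**Conclusion.** The point holds in a limited form and is minor. The article places the diary before the enrolment interview in one arm only, and its other sections imply the same for the kit and teaching without saying so. What is at stake is a possible arm-specific reporting difference in recalled items, chiefly prior PPH in one secondary model and in any matching that uses it.

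If prior PPH is asked after the teaching, and if the teaching adds 2 to 5 points of false history, the adjusted PPH risk ratio would be biased by roughly 2% to 9% in the kit's favour at a true prevalence of 10%. Both conditions are assumptions. If recall is unaffected, there is no bias from this source.

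**What to change.** In Delivery of the integrated neonatal care kit and in Data collection and data management, state one order for both arms: screening, consent, full enrolment questionnaire, and only then the LHW's hand-over and teaching (standard of care in control clusters). Ask parity, prior C-section, prior PPH and antenatal care to date in that interview, and use those answers for the history covariates and the matching variables. Newborn sex, gestational age at birth and month of birth continue to come from birth data. If field practice already follows this order, correcting the text is enough.

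The cost is a change of sequence within an existing visit and a line in data-collector training, with no added visit or staff. There are two limits. Interviewers remain unblinded. Enrolment is also under way, so women already enrolled keep the earlier order: record the date of the change in each cluster and add a sensitivity analysis of the PPH and matched analyses by collection order.
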